### Ethics

This study is conducted in accordance with the principles of the Declaration of Helsinki and Good Clinical Practice guidelines. The study protocol was approved by the Ethics Committee (METC) of the St. Antonius Hospital Nieuwegein (R-09.17A). Written informed consent will be obtained from all patients, before randomization.

### Safety and quality control

#### Data Safety Monitoring Board

The Data Safety Monitoring Board (DSMB) is composed of 4 members: 2 independent vascular surgeons and 2 independent interventional radiologists. None of the 4 members is working in one of the hospitals that will include patients. The role of the DSMB is to review safety and to make recommendations regarding the conduct of the study to the steering committee and to the accredited METC that approved the study protocol.

#### Adverse and serious adverse events

Adverse events (AE) are defined as any undesirable experience occurring to a participant during the study, whether or not considered related to the investigational device. This definition includes events occurring during hospital stay right up to 30 ± 7 days of follow-up. Underlying disease that was present at the time of enrollment is not reported as an AE, but any increase in the severity of the underlying disease will be reported as an AE.

All AEs will be monitored from the time of enrolment through the 30-day follow-up visit. AEs can be classified as moderate or serious and will be recorded on the case record forms (CRFs). A description of the event, including the start date, end date, whether device-related, any action taken, and the outcome will be provided along with the investigator's assessment of the relationship between the AE and the study treatment.

A serious adverse event (SAE) is any untoward medical occurrence or effect that at any dose results in death, or that;

• is life-threatening at the time of the event;

• requires hospitalization or prolongation of an existing inpatient's hospitalization;

• results in persistent or significant disability or incapacity; or

• necessitates an intervention to prevent a permanent impairment of a body function or permanent damage to a body structure.

Clinical events to be considered and reported as SAEs include:

• death

• myocardial infarction

• stroke

• bleeding complication requiring interruption or ending of thrombolysis

• bleeding complication requiring surgical intervention

• bleeding complication requiring transfusion

A moderate adverse event (MAE) is any untoward medical occurrence or effect that at any dose will not lead to death, or

• life-threats,

• significant disability or incapacity,

• require hospitalization or prolongation of an existing inpatient's hospitalization, or

• necessitate an intervention to prevent a permanent impairment of a body function or permanent damage to a body structure.

Clinical events to be considered and reported as MAEs include:

• groin hematoma,

• bleeding complication not requiring interruption or ending of thrombolysis, surgical intervention, or

• transfusion.

Data on SAEs and MAEs will be reported to the DSMB and to the accredited METC via the "Toetsingonline" website of the website of the Central Committee on Research inv. Human Subjects (CCMO, ccmo.nl).

### Statistical analysis

#### Intention-to-treat

The analysis will be performed in accordance with intention-to-treat principle.

#### Sample size calculation

The assumption has been made that the mean duration for successful standard thrombolytic treatment of infrainguinal native arteries or bypass grafts is 2.5 ± 1 day, based on retrospective series from the St. Antonius Hospital, Nieuwegein. Given a power of 90% and a 2-tailed significance of 5%, a 2-armed randomized trial including 26 patients in each arm will be needed to prove a significant reduction in therapy time (12 hours or more) with US-accelerated thrombolysis compared with standard thrombolysis. Taking into account 5% to 10% dropouts in each arm, 30 patients need to be included in each study arm. We will analyze the primary outcome by means of Kaplan-Meier and Log-rank test. The sample size calculation is also based on this premise. We will assess imbalance in prognostic factors as a secondary analysis by means of Cox-proportional Hazards multivariate analysis.

An interim analysis on the primary end point (ie, efficacy) will be performed after 50% of patients have completed their follow-up. The Peto approach will be followed, meaning that the study will only be stopped for beneficial effects in case of a *P *< .001 [15]. The study will not be stopped in case of futility. End points in blinded groups will be assessed by the DSMB.

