## Discussion

Several treatment strategies have focused on accelerating thrombolytic therapy to improve its effectiveness and to reduce treatment time and, therefore, adverse effects. US-accelerated thrombolysis, which involves the simultaneous delivery of low-intensity US and a thrombolytic agent into a thrombosed vessel, has been shown to reduce therapy time. The DUET study is designed to compare US-accelerated thrombolysis with standard thrombolysis in patients with recently thrombosed infrainguinal native arteries or bypass grafts.

Only patients with acute lower limb ischemia in class I and IIa, according to the Rutherford classification, will be included in our study, because catheter-directed thrombolysis is the initial treatment chosen in patients with viable or minimally threatened lower limbs. Immediate surgical revascularization is indicated in most patients with acute lower limb ischemia class IIb and III; therefore, these patients will be excluded from the study.

Prolonged thrombolysis therapy might be expected in clots older than 1 week. Most clots that are less than 1 week old can be rather easily and quickly treated with standard catheter-directed thrombolysis or thrombosuction. The additional value of the more expensive US-accelerated thrombolysis in these thrombi may be argued and these are therefore excluded from this study.

Randomization is stratified according to whether a native artery or a bypass graft is occluded, because it has been shown that thrombolysis of a bypass graft will lead to better outcome than thrombolysis of a native artery.

To test our hypothesis, a control angiography should be performed every 12 hours. Therefore, our sample size calculation is based on a reduction in therapy time of 12 hours or more. Control angiographies at 8:00 a.m. and at 8.00 p.m. would have been sufficient. However, in our study protocol we have incorporated an extra control angiography at 2.00 p.m. to measure our primary outcome more precisely and to reduce any unnecessary exposure to thrombolytics in our study participants.

Two vascular surgeons and 2 interventional radiologists from 2 nonparticipating centers will review all angiographies independently. The vascular surgeons and the interventional radiologists will be blinded for patient characteristics and for the results of the initial reports. They will be asked to classify the degree of lysis, ranging from no lysis, partial lysis, to complete lysis (>95% lysis).

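### With ± 1 day read as an SD, the printed inputs do not give 26 patients per arm: power for a 12-hour reduction is roughly 40–60%, not 90%

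*Protocol article*

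**What the plan says.** All the inputs are in the protocol article under Sample size calculation.

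- Control arm: "the mean duration for successful standard thrombolytic treatment of infrainguinal native arteries or bypass grafts is 2.5 ± 1 day", taken from a retrospective single-hospital series. The spread is not labelled.
- Error rates: "Given a power of 90% and a 2-tailed significance of 5" per cent.
- Effect and result: a two-arm trial "including 26 patients in each arm will be needed to prove a significant reduction in therapy time (12 hours or more").
- Dropout: "Taking into account 5% to 10% dropouts in each arm, 30 patients need to be included in each study arm".
- Test: "We will analyze the primary outcome by means of Kaplan-Meier and Log-rank test", followed by "The sample size calculation is also based on this premise". No hazard ratio, event count or time distribution is printed.

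The Discussion repeats the effect size, saying that "our sample size calculation is based on a reduction in therapy time of 12 hours or more". It does not repeat the figure of 26 or the power. The Hypothesis and Study objectives sections also treat 12 hours as the smallest reduction of interest.

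**The concern.** A 12-hour difference is 0.5 day. Against a spread of 1 day that is half a standard deviation, and 26 per arm is far too few to detect half a standard deviation with 90% power. The sentence linking the calculation to the log-rank test does not settle the matter, because a mean with a spread is not a log-rank input and the conversion is not shown.

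The primary endpoint's power claim is at stake. The stated purpose is to demonstrate a gain of at least 12 hours. If the true gain is 12 hours and power is near one half rather than 90%, a non-significant result says little, yet readers who trust the 90% would take it as evidence against the device.

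**Working it through.** **Inputs (Sample size calculation).** Difference δ = 12 h = 0.5 day; SD σ = 1 day (assumed reading of ±); two-sided α = 0.05, z = 1.960; power 90%, z = 1.2816. So (1.960 + 1.2816)² = 10.507. The one interim look at P < .001 has a negligible effect on the sample size.

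**1. Trying to reproduce 26 by comparing two means.**
n per arm = 2σ² × 10.507 / δ² = 2 × 10.507 / 0.25 = 84.1. With the noncentral t it is 85.03, so about 85.
Looser settings do not reach 26 either: one-sided 5% gives 69, 80% power gives 63, and the one-sample formula gives 10.507 / 0.25 = 42.03.

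**2. Power at the planned size, two means.**
At 26 per arm, the normal approximation gives 0.5 / √(2/26) − 1.960 = 1.803 − 1.960 = −0.157, or 43.8%. The noncentral t gives 42.4%. At 30 per arm it gives 47.8%.
An observed difference of exactly 12 hours with 30 per arm and SD 1 gives t = 0.5 / √(2/30) = 1.94 on 58 degrees of freedom, P = 0.058.

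**3. Log-rank by formula.** A Weibull distribution with mean 2.5 and SD 1 (coefficient of variation 0.4) has shape 2.70. Shortening the mean to 2.0 days by a common factor gives a hazard ratio for reaching flow of (2.5/2.0)^2.70 = 1.82.
Schoenfeld events = 4 × 10.507 / (ln 1.825)² = 42.03 / 0.3618 = 116.2, about 58 per arm if everyone reaches flow. Freedman's formula gives 124 events, or 62 per arm.
Power with 52 events = Φ(√52/2 × 0.6015 − 1.960) = Φ(0.209) = 58%.

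**4. Log-rank by simulation.** Every patient reaches flow and the means are 2.5 and 2.0 days. There were 3,000 runs at 26 and 30 per arm and 800 at 85.

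| Time distribution | 26 per arm | 30 per arm | 85 per arm |
|---|---|---|---|
| Normal, SD 1 in both arms | 37% | 44% | 86% |
| Gamma, SD 1 in both arms | 35% | 38% | 75% |
| Gamma, times scaled by 0.8 | 49% | 55% | 93% |
| Lognormal, SD 1 in both arms | 36% | 40% | 80% |
| Lognormal, times scaled by 0.8 | 48% | 54% | 94% |
| Lognormal, shifted by 0.5 day | 35% | 37% | 81% |
| Weibull, times scaled by 0.8 | 55% | 62% | 97% |

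From normal to Weibull the range is about 37–55% at 26 per arm and 44–62% at 30. A few skewed shapes fall slightly lower. Rounding times up to the 8 a.m., 2 p.m. and 8 p.m. angiographies changes the 26-per-arm figures by less than 4 percentage points.

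**5. What would give 26.**
- Larger difference: 2 × 10.507 / 0.90² = 25.9, so about 0.90 day by the normal approximation. By noncentral t the detectable difference at 26 per arm is 0.917 day, and 0.917 × 24 = 22 hours.
- Smaller SD: 2 × 10.507 × (0.55/0.5)² = 25.4, so an SD of about 0.55 day.
- Larger hazard ratio: exp(2 × √10.507 / √52) = exp(0.899) = 2.46 with 52 events.

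The article states none of these.

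**6. Dropout step.** 26 / 0.90 = 28.9, so 30 per arm covers 10% dropout. This step is sound.

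**The case against.** The strongest counter-argument is that the article never says what ± 1 day is. Simulating the log-rank test for a 12-hour shift under other readings gives about 90%: with ± 1 day as roughly two SDs (normal, SD 0.5), power is 91% at 26 per arm and 94% at 30; with ± 1 day as a full range (uniform), it is 89% and 93%. The figure of 26 could therefore come from an ambiguous spread rather than from faulty arithmetic. This stands as a reason to keep the conclusion conditional. It does not remove the point, because nothing in the article supports those readings and a mean ± value is ordinarily an SD. Read as a standard error, the SD would be larger and the shortfall worse.

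A second argument is that a condensed article may leave the hazard ratio and event count to the full protocol. That is fair, and their absence alone is no finding. The finding is that the printed inputs, on their usual reading, conflict with the printed result.

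Several stronger readings are tempting but not supported:

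- A reader might infer that the trial's power is 42% and that it needs 85 per arm. Those are two-means figures; the plan names the log-rank test, for which the answer depends on the time distribution.
- A reader might infer that the trial would more likely than not miss a true 12-hour gain. Under the Weibull case, log-rank power is 55% at 26 per arm and 62% at 30, so that cannot be said in general.
- A reader might convert 2.5 to 2.0 days into a hazard ratio of 1.25 with exponential times, needing about 845 events. That makes the SD equal to the mean, 2.5 days, which contradicts the stated spread.

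**Conclusion.** The point holds, conditional on ± 1 day being an SD. On that reading the stated 90% power for a 12-hour reduction is not delivered by 26 or 30 per arm under any calculation tried. Power is roughly 40–60%, and the log-rank test would need about 58 per arm at best and more under less favourable distributions.

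These log-rank figures assume that every patient reaches flow, which is generous. The 2.5-day mean describes successful treatments only, while the intention-to-treat analysis keeps technical failures and conversions to surgery. The article gives no failure rate, so this loss is not quantified, but fewer events mean less power. An expected effect above 12 hours does not rescue the claim, because 12 hours is the declared minimum.

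This must be corrected, since it is the power statement for the primary endpoint.

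**What to change.** In Sample size calculation, say what ± 1 day denotes and print the hazard ratio, expected number of patients reaching flow, and spread actually used.

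If ± 1 day is not an SD and the inputs used do support 26 per arm, printing them resolves the point.

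If it is an SD, replace the 90% claim with what 60 patients deliver after the planned dropout allowance. With 26 evaluable per arm, that is 90% power for about 22 hours (0.92 SD, two means) or for a hazard ratio of about 2.46 with 52 events, and roughly 40–60% power for 12 hours. Bring the Discussion's statement that the calculation rests on 12 hours into line with the corrected figures.

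The cost is a rewritten paragraph and one aligned sentence. No extra patients and no change to trial conduct are required; the stated power becomes less favourable.

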### Intervention

#### Group A (standard thrombolysis)

Standard thrombolysis will be performed with use of a 5F UniFuse Infusion catheter (AngioDynamics, Queensbury, NY, USA) with a working length of 90 cm, with infusion holes around the circumference of the distal 10 cm to 50 cm of the catheter. Access sites may be the contralateral common femoral artery, the ipsilateral common femoral artery, or a brachial approach.

During the initial angiography, the catheter will be navigated over a guidewire and positioned in such way that the entire distal segment with the infusion holes is in the thrombosed segment. At standardized intervals, a control angiography will be performed. During each control angiography, the distal part of the thrombolysis catheter will be repositioned in the remaining thrombosed segment.

#### Group B (US-accelerated thrombolysis)

US-accelerated thrombolysis involves simultaneous delivery of low-intensity US and a thrombolytic agent into a thrombosed vessel. US-accelerated thrombolysis will be performed with use of the EKOS EndoWave system (EKOS Corporation, Bothell, WA, USA). This system consists of a 5.2F multilumen thrombolysis delivery catheter with a 106 cm or 135 cm working length and a matching US coaxial core wire with a working zone of 6 cm to 50 cm. The central lumen of the multilumen thrombolysis delivery catheter accommodates the US core. Thrombolytics will be infused through 3 drug lumens containing multiple side holes. Low-intensity (2.2 MHz), high-frequency US will be delivered over the entire length of the infusion catheter. US power and local temperature are automatically controlled by a portable control unit.

During the initial angiography, a multilumen thrombolysis delivery catheter will be navigated over a guidewire into the thrombosed segment in such a way that the US treatment zone traverses the entire thrombosed segment and the tip of the infusion catheter is located distal to the thrombosed segment. After final positioning, the guidewire will be exchanged for a matching US core wire, and thrombolytic therapy will be started. Likewise, a control angiography will be performed at standardized intervals.

If placement of the EKOS system is technically not feasible, the procedure will be defined as a technical treatment failure. The vascular surgeon or interventional radiologist, or both, may decide what alternative treatment they will start, for instance, standard thrombolysis or conversion to open surgery. The outcome of these patients will be analyzed in group B according to the intention-to-treat principles.

#### General

The primary angiography in groups A and B will be started at day 1 at 8.00 a.m. ± 1 hour for logistic reasons. After successful positioning of the thrombolysis catheter, a bolus of 250,000 IU urokinase is given and followed by a continuous infusion with a dose of 100,000 IU urokinase/h. A control angiography will be performed every 6 ± 1 hours. During the night, standard angiography will only be performed in emergencies. Angiographies will be performed the next day at 8.00 a.m. ± 1 hour; 2.00 p.m. ± 1 hour, and 8.00 p.m. ± 1 hour. A checklist is completed during each angiography.

The pressure curve from the EKOS monitor will be recorded constantly from the start of the procedure. From the start of thrombolysis until completion angiography, the ankle-brachial indices of the treated leg and a standardized pain score will be recorded every 3 hours by a nurse practitioner or surgical resident. Every day during thrombolysis, the fibrinogen concentration must be checked: if <1.0 g/L the urokinase rate must be lowered to 50,000 IU/h; if the fibrinogen concentration is <0.5 g/L, thrombolysis must be stopped. If the obstructive clot has been successfully thrombolized, any necessary additional procedure, for instance percutaneous transluminal angioplasty (PTA) of the inflow or outflow artery, is performed before the completion angiography, and again, a checklist of the last angiography is completed.

After successful thrombolysis, systemic heparin is given (25,000 IU/24 hours) and coumarin derivatives are started. Activated partial thromboplastin time (aPTT) will be measured daily during heparinization. The target international normalized ratio (INR) will be 2.5 to 3.5; if this value is reached, heparinization can be stopped.

### Data collection

Data will be collected by means of a CRF during treatment in the participating centers. The CRF will be completed prospectively during hospital admission and during follow-up. After that, the CRFs will be forwarded to the data coordinating center. There will be regular contact between the study coordinators and the participating centers.

### Follow-up

Patients are followed-up during their hospital stay. At 30 ± 7 days after thrombolysis has been completed, there is one follow-up visit in the outpatient department, including a physical examination, ankle-brachial index, treadmill test, and contrast-enhanced MRA of the treated leg, according to current guidelines [16]. During follow-up, any additional procedures, conversion to open surgery, duration and costs of hospital admission, death, distal thromboembolic complications, and other complications will be recorded.

## Discussion

Several treatment strategies have focused on accelerating thrombolytic therapy to improve its effectiveness and to reduce treatment time and, therefore, adverse effects. US-accelerated thrombolysis, which involves the simultaneous delivery of low-intensity US and a thrombolytic agent into a thrombosed vessel, has been shown to reduce therapy time. The DUET study is designed to compare US-accelerated thrombolysis with standard thrombolysis in patients with recently thrombosed infrainguinal native arteries or bypass grafts.

Only patients with acute lower limb ischemia in class I and IIa, according to the Rutherford classification, will be included in our study, because catheter-directed thrombolysis is the initial treatment chosen in patients with viable or minimally threatened lower limbs. Immediate surgical revascularization is indicated in most patients with acute lower limb ischemia class IIb and III; therefore, these patients will be excluded from the study.

Prolonged thrombolysis therapy might be expected in clots older than 1 week. Most clots that are less than 1 week old can be rather easily and quickly treated with standard catheter-directed thrombolysis or thrombosuction. The additional value of the more expensive US-accelerated thrombolysis in these thrombi may be argued and these are therefore excluded from this study.

Randomization is stratified according to whether a native artery or a bypass graft is occluded, because it has been shown that thrombolysis of a bypass graft will lead to better outcome than thrombolysis of a native artery.

To test our hypothesis, a control angiography should be performed every 12 hours. Therefore, our sample size calculation is based on a reduction in therapy time of 12 hours or more. Control angiographies at 8:00 a.m. and at 8.00 p.m. would have been sufficient. However, in our study protocol we have incorporated an extra control angiography at 2.00 p.m. to measure our primary outcome more precisely and to reduce any unnecessary exposure to thrombolytics in our study participants.

Two vascular surgeons and 2 interventional radiologists from 2 nonparticipating centers will review all angiographies independently. The vascular surgeons and the interventional radiologists will be blinded for patient characteristics and for the results of the initial reports. They will be asked to classify the degree of lysis, ranging from no lysis, partial lysis, to complete lysis (>95% lysis).

If thrombolysis of the occluded segment is successful, any hemodynamically significant underlying atherosclerotic lesion will be identified and treated. Preferably, the underlying lesion will be treated endovascularly, with PTA with or without stent placement, or both. It will be the vascular surgeon's or interventional radiologists' decision to convert to open surgery if endovascular treatment of the underlying lesion is not feasible or if thrombolysis of the occluded segment is not successful.

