### Primary endpoint

The primary end point is the duration of catheter-directed thrombolysis needed for uninterrupted flow in the thrombosed infrainguinal native artery or bypass graft with outflow through at least 1 crural artery.

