### Randomization

Central randomization will take place using a computerized randomization procedure. Block-randomization is used and stratified according to whether a native artery or a bypass graft is involved. Blinding will not be used.

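### The independent panel that reads every angiogram is asked for degree of lysis, not for the flow criterion that defines the primary endpoint of this open-label trial

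*Protocol article*

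**What the plan says.** The Primary endpoint section of the protocol article defines the outcome as the time on thrombolysis required to reach "uninterrupted flow in the thrombosed infrainguinal native artery or bypass graft with outflow through at least 1 crural artery". It has two parts: flow through the treated vessel, and run-off into at least one crural artery.

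The Randomization section states "Blinding will not be used". Under Intervention, General, a checklist is filled in at each angiography. Under Data collection, the CRF is completed in the participating centres during treatment.

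The Discussion describes an external reading: "Two vascular surgeons and 2 interventional radiologists from 2 nonparticipating centers will review all angiographies independently". These readers "will be blinded for patient characteristics and for the results of the initial reports". Their task is given as: "They will be asked to classify the degree of lysis, ranging from no lysis, partial lysis, to complete lysis (>95% lysis". The same threshold appears under Definitions for complete lysis, and complete lysis is the core of the first secondary endpoint, technical success. No section connects the panel's reading to the primary time.

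**The concern.** Whether flow is uninterrupted and a crural vessel is open is a visual judgement, made at a few fixed time points. In an open-label trial, that judgement is exposed to the expectation set out under Hypothesis, namely that ultrasound shortens lysis by 12 hours or more. An independent reading is the usual safeguard. This trial already has outside readers looking at every image without the local report, but the variable they are described as scoring is not the primary one. The safeguard is in place and, as described, does not reach the endpoint that most needs it. A modest tendency to call success one angiogram sooner in the ultrasound arm would look like a treatment effect.

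**Working it through.** The plan gives no figure on this point, so there is none to reproduce. The check has two parts.

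**1. Does the panel's variable yield the primary endpoint?**

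| | Primary endpoint | Panel reading |
|---|---|---|
| Quantity | uninterrupted flow, plus crural outflow | share of clot dissolved |
| Site | treated segment and at least one crural artery | thrombosed segment or graft (Definitions) |
| Scale | met or not met, hence a time | none, partial, complete (>95%) |
| Endpoint served | primary | first secondary (technical success) |

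Partial lysis can restore flow, so a grade of complete is not necessary for the primary criterion. More than 95% lysis of the segment says nothing about crural run-off, so it is not sufficient either. The three grades are related to the endpoint but cannot be converted into it.

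**2. How much can one early call move the result?**

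Inputs from the article:
- angiograms at 08:00, 14:00 and 20:00 (General), so gaps of 6, 6 and 12 h
- standard-arm duration 2.5 ± 1 day (Sample size calculation), so mean 60 h and SD 24 h
- target reduction 12 h; 30 patients per arm; log-rank test at two-sided 5%

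For one patient, a call one angiogram early moves the time by 6 to 12 h. That is 6/12 = 50% to 12/12 = 100% of the target.

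For the arm mean, the gap should be weighted by the time it covers, because the 12-hour night gap spans half the day:

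(6×6 + 6×6 + 12×12)/24 = 216/24 = 9 h.

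The unweighted average, (6+6+12)/3 = 8 h, understates it slightly.

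Let f be the fraction of ultrasound patients called one angiogram early. The article gives no value for f, so a range is used. The expected shift is f × 9 h: 2.25 h at 25%, 4.5 h at 50%, 9 h at 100%.

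A simulation with no true difference checked this. It used 30 per arm, mean 60 h, SD 24 h, each time rounded up to the next scheduled angiogram, every patient reaching flow, and 2,000 trials per setting:

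| f (assumed) | Mean shift, log-normal / normal times | False-positive rate, log-normal / normal |
|---|---|---|
| 0 | −0.1 / 0.2 h | 4.9% / 5.5% |
| 25% | 2.1 / 2.3 h | 6.0% / 6.6% |
| 50% | 4.7 / 4.4 h | 10.9% / 10.1% |
| 100% | 8.9 / 8.9 h | 22.9% / 23.6% |

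The simulation error near 5% is √(0.05×0.95/2000) ≈ 0.5 percentage points. The 25% row is therefore only a little above nominal, while the 50% and 100% rows are clearly above it.

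**The case against.** **Who calls the endpoint is not stated.** This is correct. That the unblinded treating team does so is inferred from the open design, the on-site checklists and CRFs, and the Discussion's mention of separate initial reports. A reader might conclude that operators demonstrably decide the primary outcome. The article supports only the weaker statement that no other source for it is described.

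**A condensed article leaves reading procedures to the full protocol.** This is partly right. The readers are "blinded for patient characteristics and for the results of the initial reports", and silence on treatment arm or image order is not evidence that these are unmasked. Nor does the article say that lysis is the only thing they score. The point rests on what is stated: the named variable is that of a secondary endpoint, and no link to the primary time is given.

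**The DSMB assesses end points in blinded groups.** That sentence closes the interim-analysis paragraph, and the DSMB section gives the board a safety and advisory role. It reads as a group-level review and does not describe a per-patient reading of flow. It could usefully be clarified.

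**PTA might create the flow that is read.** This stronger claim is tempting, because an additional procedure such as PTA "is performed before the completion angiography, and again, a checklist of the last angiography is completed". The same sentence, however, makes the procedure conditional on the clot already having been lysed successfully, and the panel sees all angiograms, not only the last. The article does not support a claim that PTA contaminates the primary time. The order matters only for choosing which image a new flow item should be scored on.

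**The panel remedy has limits.** The two catheter systems differ, so the arm may show on the images. A panel time can also differ from the actual infusion time, which is the exposure the trial wants to shorten. Both limits stand, and the fix takes account of them.

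**Conclusion.** The mismatch holds on the text: the panel's stated variable is degree of lysis, the primary endpoint is flow with crural outflow, and nothing joins the two. That the primary time rests on unblinded local calls is an inference, though the only one the article supports.

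The possible size is material. One angiogram is worth 50% to 100% of the target for a single patient. Early calls in an assumed half of the ultrasound arm would produce about 4.5 h of spurious benefit and roughly double the false-positive rate. At an assumed 25% the effect on error is slight. These figures assume that early calls occur in one arm only and that every patient reaches flow. They show how sensitive the trial is to such calls. A reader should not infer that this bias will occur, or that the trial's error rate is 10%.

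This is a weakness worth correcting because the readers and the images are already in place. It does not by itself invalidate the design.

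**What to change.** 1. Add one yes/no item to the panel's form: is there uninterrupted flow with outflow through at least one crural artery? Score it on each control angiogram taken before any additional procedure.
2. Remove arm and time identifiers as far as the catheter allows, and fix a rule for reader disagreement in advance (for example majority or consensus).
3. Define the primary time as the first angiogram that meets the criterion by panel reading. Count patients whose lysis stops without the panel criterion being met as flow not reached, and state beforehand how they enter the Kaplan-Meier analysis, because censoring them at the stop would tie censoring to the stopping decision.
4. Report the locally called time, that is the actual duration of infusion, as a sensitivity analysis.
5. Say in the text where the primary time comes from, and what the DSMB sentence means.

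Nothing in patient care changes, and the readers and images are the same. The costs are slightly more reading work, some discordance between local and panel times, some stops counted as not reached, and masking of arm that may stay incomplete.
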